#### *Primary analysis*

Changes in the CAPI score between baseline and at the 6-month follow-up will be compared for the intervention groups using ANCOVA with the site where the family was recruited used as an independent confounder.

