### Sample size

Dawe and Harnett [9] found an effect size (ES) of 0.92 using the Child Abuse Potential Inventory (CAPI) scores, in an RCT of the PuP programme in Australia with parents of children aged 3 to 8 years. This is a large change and the current study, which is being conducted with a younger population of children (under 2.5 years), should therefore be powered to detect a much smaller change.

Power calculations for the current study show that in the region of 54 women are required in each arm of the study to detect a change in the region of 0.5 ES with 80% power and 0.05 significance. Considerably more families (that is, in excess of 147 per arm) would be required to be confident of detecting a change that is smaller than this (that is, 0.45 ES). Allowing for dropout in the region of 5% [9] necessitates that approximately 114 families are recruited to the study (that is, 57 in each arm).

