### Data analysis

All data will be analysed using an intent-to-treat analysis, unless significant deviations from the intended treatment arm are detected, in which case a per protocol analysis may also be conducted. Descriptive statistical summaries (for example, medians and ranges, means and variances, or contingency tables, depending on the variable distribution and type) will be presented for the primary and secondary outcome measures at each time point. Baseline data will be scrutinised to check comparability between treatment arms and to highlight any characteristic differences between the six trial recruitment sites. Any disparities found will be added to subsequent models to compensate for these differences.

Data collected from families who were approached but refused to take part and those who dropped out will also be analysed and examined for trends (using only basic information such as consenting participant age, gender and intervention arm), alongside qualitative data concerning the reasons for dropping out. We will also investigate potential contamination between intervention groups, as described in the Randomisation section above.

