#### *Subsidiary analyses*

In a similar manner to the primary outcome measures, changes in the secondary outcome measures at baseline and at the 6-month follow-up will also be compared for the intervention groups using ANCOVA. We will also examine the differences at baseline and the immediate post-intervention follow-up period for all outcome measures.

To further investigate the effects of confounding variables, subject to the limitations of the data, we will use multi-level linear mixed modelling between intervention arms. The use of a combination of random and fixed effects, will enable us to model the impact of factors such as therapist, site, family composition and family trajectory.

We will also construct regression models to investigate the relation between the primary outcome measures (that is, CAPI) and other potential mediating variables (that is, measures of parental mindfulness and affect regulation), to address the hypothesis that the impact of the programme on the primary outcome will be mediated via the parent’s capacity for affect regulation.

Multiple imputation (MI) will be used to compensate for missing data at different assessment points. Imputation assumptions for MI will be reported and justified, and imputed data analysed as part of a sensitivity analysis.

Qualitative data will be fully transcribed and analysed thematically using NVivo 8. The limitations of the qualitative data will be assessed in terms of its credibility, transferability, dependability and confirmability [82]. This data will also be examined on a case-by-case basis in terms of the mixed-methods analysis, to better understand the reasons for the success, or otherwise, of the intervention.

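### The primary analysis is called ANCOVA but names only site, so baseline BCAPI is not a prespecified covariate

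*Protocol article*

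**What the plan says.** Under Primary analysis the protocol article has a single sentence. It takes the change in CAPI score from baseline to 6 months as the outcome and says that these changes "will be compared for the intervention groups using ANCOVA with the site where the family was recruited used as an independent confounder". Site is the one adjustment variable named. The baseline score is neither listed as a covariate nor ruled out.

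The Subsidiary analyses section carries the approach over to the other endpoints: "changes in the secondary outcome measures at baseline and at the 6-month follow-up will also be compared for the intervention groups using ANCOVA". It adds a comparison at the immediate post-intervention time point for all outcome measures. No covariate is named for either.

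The opening of the Data analysis section deals with baseline variables in general. Arms and sites are to be checked for comparability at baseline, and then "Any disparities found will be added to subsequent models to compensate for these differences". On this wording, a baseline variable enters only after an imbalance has been seen.

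The Sample size section asks for about 54 participants per arm, with the aim "to detect a change in the region of 0.5 ES with 80% power and 0.05 significance". It does not say whether the effect size is scaled by the SD of the raw score or of the change, whether the test is one- or two-sided, or whether any covariate adjustment was assumed.

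**The concern.** Every participant has a baseline score, so adjusting for it costs no data. If the analysis follows the text literally, the outcome is a change score and the model holds arm and site only. That fixes the coefficient on baseline at 1, whereas the baseline-adjusted model estimates it, and for two measurements with equal variance the true value is r. The literal analysis has two weaknesses:

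- It is less precise than the baseline-adjusted analysis for every r below 1.
- It over-corrects when the arms differ at baseline by chance: the arm that starts higher tends to show a larger fall from regression to the mean alone.

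The route by which baseline could enter, through an observed disparity, makes the covariates of the confirmatory model depend on the data. Two analysts working from this text could fit different primary models and report different estimates. The same would apply to each secondary outcome.

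**Working it through.** **Inputs**

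- 54 analysed per arm, effect size 0.5, 80% power, alpha 0.05: Sample size section.
- Outcome is the change, and site is the one named covariate: Primary analysis section.
- Correlation r between baseline and 6-month scores: not given. The nearest figures, under Primary outcome measures, are test-retest values for the full CAPI of .91 at 1 day and .83 at 1 month. The trial interval spans a 20-week programme and a later follow-up, so r may well be lower. I take 0.3 to 0.83 as an assumed range.
- Also assumed: two-sided test, equal variances at the two time points, effect size in raw-score SD units.

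**The plan's own figure**

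A two-sided two-sample t-test at effect size 0.5 needs 64 per arm for 80% power; 54 per arm gives 73%. One-sided, 54 per arm gives 83% and about 51 would be enough. So 54 does not come out of the stated inputs either way. The dropout step does reproduce: 54/0.95 = 56.8, that is 57 per arm and 114 in total. The origin of 54 is a separate matter; here it serves only as the number analysed.

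**Precision**

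With raw-score SD set to 1:

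- residual variance, change score: 2(1-r)
- residual variance, baseline-adjusted: 1-r² = (1-r)(1+r)
- ratio: 2(1-r) / [(1-r)(1+r)] = 2/(1+r), which exceeds 1 for every r below 1

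**Power**

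Noncentral t, 54 per arm, standardised effect = 0.5/√(residual variance):

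| r | Variance ratio 2/(1+r) | Change score: effect, power | Baseline-adjusted: effect, power |
|---|---|---|---|
| 0.3 | 1.54 | 0.5/1.183 = 0.423, 58.5% | 0.5/0.954 = 0.524, 77.0% |
| 0.5 | 1.33 | 0.5/1.000 = 0.500, 73.1% | 0.5/0.866 = 0.577, 84.4% |
| 0.7 | 1.18 | 0.5/0.775 = 0.645, 91.4% | 0.5/0.714 = 0.700, 95.0% |
| 0.83 | 1.09 | 0.5/0.583 = 0.857, 99.3% | 0.5/0.558 = 0.896, 99.6% |

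The loss is 18.5 points at r = 0.3, 11.3 at 0.5, 3.6 at 0.7 and 0.3 at 0.83.

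**If the effect size is in change-score SD units**

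Change-score power is then 73.1% whatever r is. Adding baseline raises the standardised effect to 0.5/√((1+r)/2), which gives 89.1%, 84.4%, 79.7% and 76.8% at the same four values of r. The direction is the same.

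**Chance imbalance**

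Given a baseline difference D between arms, the expected follow-up difference is the treatment effect plus rD. Subtracting D leaves the treatment effect minus (1-r)D. One standard error of D with 54 per arm is √(2/54) = 0.19 SD. A difference of that size moves the change-score estimate by:

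- r = 0.5: 0.5 × 0.19 = 0.096 SD, or 19% of the 0.5 SD target
- r = 0.7: 0.3 × 0.19 = 0.058 SD, or 12% of the target

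The baseline-adjusted estimate removes this shift.

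**The case against.** The strongest reply is that the text does not exclude baseline. ANCOVA ordinarily implies a continuous covariate and site is categorical, so a reader could take the baseline score as understood. A condensed article may leave the full covariate list to an analysis plan that is not shown here. The sentence on secondary outcomes names no covariates at all, so it cannot show that baseline was dropped. This stands: it would be wrong to say that the plan analyses change adjusted for site alone, or that it rejects baseline adjustment. What remains is that the one sentence defining the primary model lists site and not baseline, while the neighbouring general rule makes baseline adjustment depend on an observed disparity.

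That rule is also a partial answer to chance imbalance, since a visible difference in BCAPI would lead to adjustment. It does not recover precision when the arms look balanced, and it leaves the choice of model to the data.

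It is also right that a change score is no fault in itself. Once baseline is in the model, change and follow-up score give the same treatment estimate.

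Finally, the size of the loss rests on a correlation that the document does not report. At the only published anchor, .83, the loss is a fraction of a percentage point.

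**Conclusion.** The point holds as a matter of specification. Baseline BCAPI is not a prespecified covariate in the primary model. Followed literally, the plan gives a less precise estimate that is more exposed to chance baseline differences than one it could have at no cost. The direction is certain for any r below 1. The size is not: under the assumptions above, the power loss runs from about 18 points at r = 0.3 to 0.3 points at r = 0.83.

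Three stronger conclusions that a reader might draw are not supported.

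- **That 54 per arm delivers 80% power only with baseline adjustment.** At r = 0.6 the change score alone has 82% power, and at r = 0.3 the adjusted analysis has only 77%. In raw-score SD units the 80% threshold falls at r of about 0.58 for the change score and 0.39 for the adjusted analysis, so adjustment is neither necessary nor sufficient.
- **That small numbers per centre make imbalance in the primary contrast likely.** That contrast pools all six centres, with about 57 randomised per arm and site in the model. The relevant standard error of the baseline difference is the pooled 0.19 SD.
- **That the literal analysis is biased.** Over repeated randomisation a change-score comparison is unbiased. The shift of (1-r)D is conditional on the imbalance that happens to occur.

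This is a free improvement and a clarification. It does not invalidate the design.

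**What to change.** Replace the primary-analysis sentence with one that prespecifies ANCOVA with treatment arm, baseline BCAPI abuse risk score and centre, fitted whatever baseline imbalance is observed. The outcome may be the 6-month score or the change from baseline. Naming the BCAPI abuse risk score also settles which score is meant, since the analysis section says CAPI.

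Use the same form, with each outcome's own baseline and centre, for the secondary outcomes and for the immediate post-intervention time point. Models that add other baseline variables because of an observed disparity should be labelled as sensitivity analyses.

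The cost is a sentence or two of text. No new data are needed, and the Trial status section says that recruitment is only just starting, so the change can be made before any outcome is seen.

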#### *Subsidiary analyses*

In a similar manner to the primary outcome measures, changes in the secondary outcome measures at baseline and at the 6-month follow-up will also be compared for the intervention groups using ANCOVA. We will also examine the differences at baseline and the immediate post-intervention follow-up period for all outcome measures.

To further investigate the effects of confounding variables, subject to the limitations of the data, we will use multi-level linear mixed modelling between intervention arms. The use of a combination of random and fixed effects, will enable us to model the impact of factors such as therapist, site, family composition and family trajectory.

We will also construct regression models to investigate the relation between the primary outcome measures (that is, CAPI) and other potential mediating variables (that is, measures of parental mindfulness and affect regulation), to address the hypothesis that the impact of the programme on the primary outcome will be mediated via the parent’s capacity for affect regulation.

Multiple imputation (MI) will be used to compensate for missing data at different assessment points. Imputation assumptions for MI will be reported and justified, and imputed data analysed as part of a sensitivity analysis.

Qualitative data will be fully transcribed and analysed thematically using NVivo 8. The limitations of the qualitative data will be assessed in terms of its credibility, transferability, dependability and confirmability [82]. This data will also be examined on a case-by-case basis in terms of the mixed-methods analysis, to better understand the reasons for the success, or otherwise, of the intervention.

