### Data-collection process

Data will be collected by a researcher who is blind to study arm, in the respondent’s home or at a drug treatment centre. Study participants will be requested not to disclose their group allocation to the researcher, and loss of blinding will be recorded and taken into account at the analysis stage. The data will comprise a range of self-report questionnaires that are robust to loss of blinding, and independent observations of the parent and infant, which will be rated externally to the research team. The researcher will provide assistance with the completion of self-report questionnaires where this is required. Data will be collected at baseline, immediately post-intervention and at the 6-month follow-up.

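### The primary ANCOVA is an observed-case analysis: families without a 6-month score are left out even when their post-intervention score has been collected

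*Protocol article*

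**What the plan says.** Under Data analysis, the article states: "All data will be analysed using an intent-to-treat analysis, unless significant deviations from the intended treatment arm are detected". In that event a per-protocol analysis may be added.

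Under Primary analysis: "Changes in the CAPI score between baseline and at the 6-month follow-up will be compared for the intervention groups using ANCOVA", with recruitment site also in the model. No other time point enters. The article writes CAPI here; the instrument named under Primary outcome measures is the brief form, BCAPI, and that is the score meant below.

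Under Data-collection process: "Data will be collected at baseline, immediately post-intervention and at the 6-month follow-up". So two follow-up scores are scheduled for each family.

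Under Subsidiary analyses, three sentences bear on the point:
- The earlier follow-up gets its own comparison: "We will also examine the differences at baseline and the immediate post-intervention follow-up period for all outcome measures".
- A mixed model is planned to look at confounding: "subject to the limitations of the data, we will use multi-level linear mixed modelling between intervention arms".
- On missing data, "Multiple imputation (MI) will be used to compensate for missing data at different assessment points", but with "imputed data analysed as part of a sensitivity analysis".

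Under Sample size, the only attrition figure is about 5%, taken from the earlier Australian trial in parents of children aged 3 to 8.

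**The concern.** A family with no 6-month score has no baseline-to-6-month change, so it can enter the primary ANCOVA only if that score is imputed. The article places imputed data in a sensitivity analysis, so such a family contributes nothing to the primary estimate. Its post-intervention score, probably the best collected predictor of the missing value, is not used there either.

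Taking the ANCOVA to include baseline score, arm and site, an observed-case analysis is unbiased if 6-month missingness depends only on those three. It is biased if, given those three, missingness also depends on how the family was doing at programme end. That is plausible in this setting. Participants are in treatment for a drug or alcohol problem, the entry criteria foresee children being removed during the study, and the arms differ greatly in contact intensity, so the reasons for loss could differ by arm. At stake are the headline estimate and, to a lesser degree, its precision.

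**Working it through.** **1. The plan's own figures.** Sample size gives 54 evaluable per arm and 5% dropout. 54 / 0.95 = 56.8, so 57 per arm and 114 in total, as stated. The 54 itself does not follow from ES 0.5, 80% power and two-sided 0.05 (63 to 64 per arm). That is a separate matter and does not affect this point.

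**2. Families left out.** The number observed per arm is 57 × (1 − loss). At 5% it is 54.2, so about 3 per arm (114 × 0.05 = 5.7 in total) are outside the primary analysis. Higher losses are assumptions: 10% leaves 51.3, 20% leaves 45.6 and 30% leaves 39.9 per arm.

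**3. Power, and how much the remedy recovers.** This uses a two-sided t-test at 0.05, ES 0.5, with no gain from the baseline covariate. With all 57 per arm observed, power is 75.4%.

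For the remedy, assume correlations of 0.6 (baseline with post), 0.5 (baseline with 6 months) and 0.7 (post with 6 months). The partial correlation of the two follow-up scores given baseline is (0.7 − 0.6 × 0.5) / √((1 − 0.36)(1 − 0.25)) = 0.577, and its square is 0.333. If every family lost at 6 months has a post-intervention score, the effective number per arm is n_obs / (1 − loss × 0.333).

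| Loss | Observed per arm | Power, observed-case | Effective per arm | Power, both follow-ups |
|---|---|---|---|---|
| 5% | 54.2 | 73.2% | 55.1 | 73.9% |
| 10% | 51.3 | 70.8% | 53.1 | 72.3% |
| 20% | 45.6 | 65.6% | 48.9 | 68.7% |
| 30% | 39.9 | 59.7% | 44.3 | 64.4% |

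This is the favourable case, since some lost families will have no post-intervention score. The gain is 0.7 points at 5% and 4.7 points at 30%.

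**4. Bias, by large-sample simulation.** All inputs are assumed: a true effect of −0.50 SD at both follow-ups, the same correlations, and 6-month loss following a logistic model with slope 1 per SD of the post-intervention score (worse scores lost more often). Estimates from the observed-case ANCOVA:

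| Where loss depends on the score | 5% loss | 20% loss | 30% loss |
|---|---|---|---|
| Both arms | −0.49 | −0.48 | −0.47 |
| Intervention arm only | −0.52 | −0.56 | −0.60 |
| Control arm only | −0.48 | −0.42 | −0.39 |

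Imputation using the post-intervention score returns about −0.50 in every cell. In the two one-arm scenarios, total loss at 20% to 30% differs between arms by only about 3 to 6 percentage points, so similar attrition rates would not rule the bias out.

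**The case against.** The strongest reply is that the article never calls the primary analysis complete-case. It gives one sentence on the ANCOVA, and the definition of the analysis set, the content of the imputation model and missing-not-at-random scenarios usually belong in the analysis plan. The last part stands: their absence from an article is no fault. But the role of imputation is not left open. The article assigns it to a sensitivity analysis, and nothing else brings a family without a 6-month score into the primary estimate.

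Four stronger readings are tempting, and the article does not support them.

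- A reader might infer that the plan contradicts its own intent-to-treat statement. The sentence contrasts intent-to-treat with departures from the intended arm, so it is about analysing families as allocated. The observed-case ANCOVA does that; what it does not do is include everyone randomised.
- A reader might infer that the post-intervention score is ignored altogether. It has its own subsidiary comparison, and the subsidiary mixed models mention family trajectory. It is absent from the primary analysis only.
- A reader might take heavy or outcome-related loss as established. The only figure given is 5%. BCAPI is self-reported and can be collected at home or at a treatment centre, and the intervention continues if a child is removed. Higher or informative loss is an assumption.
- A reader might take the fall in power with attrition as what the remedy would restore. Most of that fall is unrecoverable.

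It is also fair to say that the planned imputation analysis could reveal a shift, and that a repeated-measures model also rests on a missing-at-random assumption and gains nothing from families with no follow-up score. Both points stand. They limit the claim for the remedy, but they are not reasons to keep the less robust analysis as primary.

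**Conclusion.** The point holds as a worthwhile improvement rather than a serious flaw. As written, the primary estimate is based on families with an observed 6-month score and leaves collected outcome data unused.

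At the planned 5% loss this concerns about 3 families per arm. Bias is about 0.01 to 0.02 SD under the assumptions above, and the power at stake is under 1 point. At an assumed 20% to 30%, bias is about 0.02 to 0.03 SD if the mechanism is the same in both arms. It is about 0.06 to 0.11 SD, in either direction, if the mechanism operates in one arm only. Recoverable power is then about 3 to 5 points.

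These sizes rest on assumed correlations, an assumed dropout slope and an equal effect at both follow-ups; none of these is in the article. The reading of the primary analysis as observed-case does not depend on them.

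**What to change.** Make the primary analysis a linear mixed model for repeated measures on BCAPI at post-intervention and 6 months. Include arm, visit and arm-by-visit, with baseline BCAPI and centre each interacting with visit. The primary contrast is the 6-month difference between arms. Multiple imputation with the post-intervention score in the imputation model, promoted to primary, would serve the same purpose.

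Keep the observed-case ANCOVA as a sensitivity analysis and add one that departs from missing at random, for example by shifting imputed scores for lost families in the unfavourable direction. State that the primary result relies on missing at random, and that families with no follow-up score are represented only through that assumption or through imputation. Add a sentence making clear that intent-to-treat refers to analysis by allocated arm, and say which randomised families contribute.

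The cost is a change of wording and a slightly more complex model. No new data are needed, since both follow-ups are already scheduled, and the article reports that recruitment is only starting. When nothing is missing the answer is close to that of the ANCOVA, and identical only if all covariate effects vary by visit, as specified above.
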